#### Sample Size

This study will aim to recruit and screen 60 eligible patients to enroll and randomize 12 participants in a 2:1 ratio. Sample size was influenced by expected confidence interval widths for the primary outcome (technical performance of the rhPDGF-BB-enhanced collagen implant for treatment of complex perianal fistulas). Assuming that all 8 participants assigned to the intervention arm will achieve successful implementation of the treatment, the lower bound of a Clopper-Pearson 95% confidence interval would be 0.63, indicating high confidence that the treatment does not have a low probability of successful implementation. Sample size was also influenced by the efficacy outcome of healing at 3 months. Based on the prior work in the literature, we assume that the routine care arm (across the expected distribution of routine care procedures) will achieve 50% healed at 3 months (2/4 healed). If 7 of the 8 intervention arm patients achieve healing, the expected lower bound of a Carlin-Louis 95% confidence interval for the differences in proportions healed would be about −0.14, indicating high confidence that the intervention does not cause substantial harm. Furthermore, if all 8 intervention arm patients achieve healing, the expected interval lower bound will be −0.01, such that there is high confidence of treatment benefit.

We assumed that study dropout before Month 3 will not occur, and that crossover into the intervention arm will not occur until after ascertainment of Month 3 outcomes. The time-to-healing will be considered for secondary analyses and likely have slightly higher power assuming that patient-reported data is accurate and high quality, as it achieves higher granularity to assess healing than the binary outcome of healing at Month 3 follow-up. Likewise, exploratory analyses including crossover patients may improve power for assessing the primary outcome. Other secondary endpoints and subgroup analyses are exploratory in nature, and we did not perform formal power analyses for these.

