#### Secondary and Tertiary Outcomes Analysis

The secondary efficacy and safety endpoints will be analyzed for all randomized participants, as appropriate. Analyses will not be dependent on the findings of the primary endpoint. The first secondary endpoint considers all treatment-related adverse events and the proportion of participants with such events by arm will be analyzed/reported in the same way as the primary endpoint. The proportion will then be compared across arms using Fisher’s Exact test. If there are at least two participants with multiple treatment-related adverse events, a Mann-Whitney test will compare the number of adverse events per participant across arms.

The next secondary endpoint is fistula healing at Month 3 measured as a binary variable. The probability of healing in each arm will be calculated as the proportion of randomized participants per arm that are diagnosed as completely healed by a clinical evaluation of no visible drainage from the external opening at the Month 3 follow-up visit. The endpoint will be modeled as the outcome in a logistic regression model, conditioning on the treatment arm and baseline etiology. The effect will be presented as an adjusted odds ratio with a 95% confidence interval, as well as the marginal risk ratio after performing standardization. A p-value less than 0.05 will be considered statistically significant, but interpretation will be primarily focused on the 95% confidence interval. Residuals will be inspected to inspect model fit and validity of the homoscedasticity assumption. If model fit is poor, a Fisher’s Exact test will be used in place of logistic regression. Missing data are expected to be limited but will be handled using multiple imputation. Individuals who are lost to follow-up before Month 3 will also be included via the multiple imputation procedure, considering plausible imputations conditional on their baseline and Month 1 follow-up assessments, as well as weekly symptom data. The primary analysis will be modified intention-to-treat (ITT) based on randomized arm, as the investigational product is not available to patients who are not randomized to treatment before the Month 3 outcome assessment. It will be modified ITT in the sense that only participants who receive the investigational intervention will be analyzed as part of the intervention arm; this is necessary as some exclusion criteria cannot be assessed until the time of surgery.

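### Sample Size reads a 95% interval with lower bound −0.01 as high confidence of benefit, although that interval narrowly includes no difference

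*Protocol article*

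**What the plan says.** The Sample Size section plans to "enroll and randomize 12 participants in a 2:1 ratio", which gives 8 intervention and 4 control patients. It assumes that half of the controls, 2 of 4, are healed at Month 3, and gives the lower bound of a Carlin-Louis 95% interval for the difference in proportions healed under two intervention results.

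- 7 of 8 healed: lower bound about −0.14, read as "indicating high confidence that the intervention does not cause substantial harm".
- 8 of 8 healed: "the expected interval lower bound will be −0.01, such that there is high confidence of treatment benefit".

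The Statistical analysis section sets α = 0.05, with two-tailed p-values as appropriate, and ranks 95% confidence intervals above p-values. For Month 3 healing, Secondary and Tertiary Outcomes Analysis repeats this: "A p-value less than 0.05 will be considered statistically significant, but interpretation will be primarily focused on the 95% confidence interval". The planned model is logistic regression on arm and etiology, with Fisher's exact test as the fallback if the model fits poorly.

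**The concern.** A 95% interval whose lower bound is below zero does not exclude no difference. The 8/8 sentence therefore draws a conclusion that its own number does not support under the plan's stated way of reading results. The section also says that the healing outcome influenced the sample size, so the sentence is part of the stated justification for 12 participants.

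Two things are at stake. The design is credited with a property it lacks at the assumed control result. And a later reader could cite the protocol to present 8/8 versus 2/4 as demonstrated efficacy.

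**Working it through.** **Inputs** (all from Sample Size): 8 intervention and 4 control patients; 2/4 controls healed; 7/8 or 8/8 intervention patients healed; no dropout before Month 3.

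**Step 1. Reproduce the stated bounds.** The article does not define the Carlin-Louis interval further. I took it as the equal-tailed 95% posterior interval for the difference, with independent uniform Beta(1,1) priors. With x of n healed, the posterior is Beta(x+1, n−x+1).

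| Result | Posteriors | 95% interval | Stated lower bound |
|---|---|---|---|
| 7/8 v 2/4 | Beta(8,2) v Beta(3,3) | −0.145 to 0.717 | about −0.14 |
| 8/8 v 2/4 | Beta(9,1) v Beta(3,3) | −0.008 to 0.788 | −0.01 |

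Both figures reproduce, which supports this reading of the method.

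**Step 2. Why 8/8 v 2/4 includes zero.** The posterior probability that control healing exceeds intervention healing is the mean of p⁹ when p follows Beta(3,3):

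B(12,3) / B(3,3) = [2/(14×13×12)] / (1/30) = 60/2184 = 0.0275.

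The posterior probability of any benefit is therefore 1 − 0.0275 = 0.9725. The lower tail beyond zero holds 2.75%, slightly more than the 2.5% that a 95% interval cuts off, so the lower bound falls just below zero.

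**Step 3. Fallback test.** With 2 non-healers among 12 patients, the chance that both are among the 4 controls is C(4,2)/C(12,2) = 6/66 = 0.091. The other two possible tables have probabilities 32/66 and 28/66, so neither is as extreme and the two-sided Fisher p is also 0.091. For 7/8 v 2/4 it is 0.24.

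**Step 4. What would exclude zero.** With 8/8 healed in the intervention arm:

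| Controls healed | 95% lower bound | Fisher p (two-sided) |
|---|---|---|
| 0/4 | +0.33 | 0.002 |
| 1/4 | +0.14 | 0.018 |
| 2/4 (assumed) | −0.01 | 0.091 |
| 3/4 | −0.13 | 0.33 |

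**Step 5. How often the lower bound exceeds zero.** With 50% control healing, P(0 of 4) = 1/16 and P(0 or 1 of 4) = 5/16. The bound exceeds zero when 7 or 8 intervention patients heal with 0 or 1 control, or 6 with 0 controls.

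- True healing 100% v 50%: the intervention result is always 8/8, so the probability is 5/16 = 31%. The Fisher test gives the same 31%.
- True healing 87.5% v 50%: P(8) = 0.344, P(7) = 0.393 and P(6) = 0.196, so (0.344 + 0.393) × 5/16 + 0.196 × 1/16 = 0.24. Fisher p < 0.05 in favor of the intervention occurs in 13%.

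**The case against.** The best defense is that zero is only just included and that the phrase has informal support. Under the same priors the posterior probability of any benefit is 0.97, and the one-sided 95% lower bound is +0.05. Other intervals for 8/8 v 2/4 exclude zero: highest-density +0.009, Wald +0.010, Newcombe +0.023, Jeffreys prior +0.036. Fisher is only the fallback. A likelihood-ratio test from the planned logistic model gives p = 0.022 unadjusted, and 0.012 or 0.017 adjusted for etiology if the 9:3 split anticipated in Randomization and Blinding occurs. Moreover, the interval that the healing analysis will report is for the adjusted odds ratio, not the Carlin-Louis difference.

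This bears on size and wording, but it does not rescue the sentence. The section quotes the Carlin-Louis 95% interval and states no posterior-probability or one-sided criterion. Nor is the logistic result firm: with 8/8 healed the model is separated, so the odds ratio is infinite and its Wald interval is unusable. The Firth version gives p of 0.053 to 0.059.

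A reader might infer three stronger criticisms. None is supported.

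- *The trial cannot show benefit.* This holds at the assumed 2/4 control result, not for every result; Step 4 shows tables that exclude zero. The probability is low, not nil.
- *The arithmetic is wrong.* Both bounds reproduce, and each is explicitly conditional on a stated result. The fault is one of interpretation.
- *The harm statement is equally wrong.* A bound of −0.14 does exclude a larger loss of healing. Whether 14 points is substantial is a judgment, and the number already stands in the sentence.

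**Conclusion.** Wrong as written; minor. At 8/8 v 2/4 the 95% interval is −0.01 to 0.79. By the plan's own emphasis on 95% intervals this is suggestive of benefit but does not establish it. If the true rates were 87.5% v 50%, the interval would exclude zero in favor of the intervention in about a quarter of trials; even if every intervention patient healed, in under a third.

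The interval figures rest on uniform priors with equal tails, the only added assumption, and one that recovers both stated bounds. The trial percentages also assume 50% control healing and no dropout, as the section does.

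Severity is limited because healing is a secondary endpoint, the Discussion calls the study a pilot and concedes that the small sample limits power for efficacy, and no stated decision rule uses the phrase. That concession does not cure the sentence; the two passages give different messages about the same comparison.

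**What to change.** In Sample Size, replace the clause that follows the −0.01 figure with wording such as:

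> the 95% interval (−0.01 to 0.79) would narrowly include no difference (posterior probability of any benefit about 0.97 under uniform priors), so this result would be suggestive of benefit but would not establish it.

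Optionally, add to the 7/8 sentence that its interval (−0.14 to 0.72) excludes a reduction in healing greater than about 14 points.

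Leave the healing analysis in Secondary and Tertiary Outcomes Analysis unchanged. A blanket statement that no conclusion of benefit will be drawn would conflict with its p < 0.05 rule, and would apply even to a result such as 8/8 v 0/4.

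The cost is one clause, or two sentences with the option. Design, enrollment, data collection and analysis do not change; the stated justification simply becomes less favorable.

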#### Primary Outcomes Analysis

The primary endpoint is technical performance of the treatment. This will be reported as the proportion of participants assigned to the treatment arm with successful implementation of the treatment (without SAEs). This will be reported along with a Carlin-Louis 95% confidence interval.

#### Secondary and Tertiary Outcomes Analysis

The secondary efficacy and safety endpoints will be analyzed for all randomized participants, as appropriate. Analyses will not be dependent on the findings of the primary endpoint. The first secondary endpoint considers all treatment-related adverse events and the proportion of participants with such events by arm will be analyzed/reported in the same way as the primary endpoint. The proportion will then be compared across arms using Fisher’s Exact test. If there are at least two participants with multiple treatment-related adverse events, a Mann-Whitney test will compare the number of adverse events per participant across arms.

The next secondary endpoint is fistula healing at Month 3 measured as a binary variable. The probability of healing in each arm will be calculated as the proportion of randomized participants per arm that are diagnosed as completely healed by a clinical evaluation of no visible drainage from the external opening at the Month 3 follow-up visit. The endpoint will be modeled as the outcome in a logistic regression model, conditioning on the treatment arm and baseline etiology. The effect will be presented as an adjusted odds ratio with a 95% confidence interval, as well as the marginal risk ratio after performing standardization. A p-value less than 0.05 will be considered statistically significant, but interpretation will be primarily focused on the 95% confidence interval. Residuals will be inspected to inspect model fit and validity of the homoscedasticity assumption. If model fit is poor, a Fisher’s Exact test will be used in place of logistic regression. Missing data are expected to be limited but will be handled using multiple imputation. Individuals who are lost to follow-up before Month 3 will also be included via the multiple imputation procedure, considering plausible imputations conditional on their baseline and Month 1 follow-up assessments, as well as weekly symptom data. The primary analysis will be modified intention-to-treat (ITT) based on randomized arm, as the investigational product is not available to patients who are not randomized to treatment before the Month 3 outcome assessment. It will be modified ITT in the sense that only participants who receive the investigational intervention will be analyzed as part of the intervention arm; this is necessary as some exclusion criteria cannot be assessed until the time of surgery.

Supplementary analysis of this secondary endpoint will consider time in weeks to achieve complete healing from baseline up to 12 weeks. This endpoint will be determined by the self-reported measure of no leakage from the weekly participant survey and will be focused on the first achievement of complete healing, as recurrence will be assessed in other outcomes. This endpoint will be analyzed using a Cox proportional hazards model, conditional on the treatment arm and Crohn’s status as outlined in the SAP. The results will be presented as an adjusted hazard ratio and a marginal hazard ratio after performing standardization. Proportional hazards will not be checked with a hypothesis test, as this is typically not a recommended procedure; instead, Kaplan-Meier curves will be calculated, and plausibility of proportional hazards will be assessed visually. If proportional hazards are violated or model fit is poor, the outcome will be compared across arms using the log-rank test. Missing data are expected to be limited, but will be handled using multiple imputation, taking the longitudinal nature of surveys into account.

The next secondary endpoint is fistula recurrence at 6 months. This will be measured as the percentage of the total number of treated participants in each arm that were diagnosed as healed at Month 3 with subsequent recurrence of the fistula by clinical evaluation of the external opening at the Month 6 follow-up visit. This is a binary endpoint which will be analyzed using the same procedures as those outlined for the binary Month 3 healing endpoint.

The final secondary endpoint is the change in the severity of symptoms at Month 3 (adjusted for baseline), which will be calculated using the ordinal scale for each question in the weekly participant survey. Scores will be compared between arms using Mann-Whitney tests. A composite variable will be calculated as defined in the SAP and analyzed using ordinal logistic regression conditional on treatment arm, baseline score, and baseline etiology. The proportional odds assumption will be assessed using a parallel line plot. A longitudinal ordinal mixed effects model with similar specification and a random intercept for study participant and a linear time term will be used to compare longitudinal symptom severity over time. Results will be presented as adjusted odds ratios and missing data will be handled using multiple imputation.

Tertiary outcomes will be reported as totals or proportions, as appropriate. Analyses of proportions retained at 3 months and 6 months will be similar to those for the primary outcome. Exploratory analyses which consider outcomes of participants who cross over into the investigational device arm will be reported separately or included in sensitivity analyses.

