### Randomization and Blinding

Randomization will occur at the baseline visit at a ratio of 2:1 intervention versus control. Randomization will be stratified to achieve balance in treatment allocation across idiopathic and CD-related fistula types. Because the total sample size is 12, randomization will be blocked using blocks of size 3 (2:1 intervention to control) within each stratum (idiopathic versus CD-related). Based on historical clinical data we anticipate enrolling 9 Chron’s participants and 3 idiopathic participants. Blinding of the patients, surgeons other than the investigator performing the procedure, and study team members assessing outcomes to study arm allocation will be employed to reduce bias in conducting study activities and evaluations. Given that the control group will be receiving a routine care procedure, the investigator who will be performing all procedures will be unblinded to the treatment assignment for each participant. To maintain blinding while assessing outcomes, clinical exams during follow-up study visits will be performed by another surgeon not involved in the initial screening visit or the procedural encounter. In the case of a serious adverse event or medical emergency in which knowledge of the treatment is necessary for the participant’s well-being or medical care, the unblinded investigator will be alerted to ensure appropriate medical management.

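### Month 3 healing: the logistic model is checked for an assumption it does not make, may give no finite treatment odds ratio at 12 participants, and falls back on an unadjusted test under an undefined rule

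*Protocol article*

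**What the plan says.** Protocol article, Secondary and Tertiary Outcomes Analysis, on healing at Month 3: "The endpoint will be modeled as the outcome in a logistic regression model, conditioning on the treatment arm and baseline etiology". The result is to be given as an adjusted odds ratio with a 95% interval and as a marginal risk ratio after standardization, with interpretation resting mainly on the interval. The model check follows: "Residuals will be inspected to inspect model fit and validity of the homoscedasticity assumption". If the fit is poor, a Fisher's "Exact test will be used in place of logistic regression". Month 6 recurrence is to be analysed in the same way.

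Three other places bear on this:
- Statistical analysis: models are to be adjusted for Crohn's status, and intervals take precedence over p-values.
- Randomization and Blinding: "randomization will be blocked using blocks of size 3 (2:1 intervention to control) within each stratum", with 9 Crohn's "participants and 3 idiopathic participants" expected.
- Sample Size: the trial is to "enroll and randomize 12 participants in a 2:1 ratio". Healing is considered at 2/4 in the control arm against 7/8 or 8/8 in the intervention arm, using a "Carlin-Louis 95% confidence interval for the differences in proportions healed".

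**The concern.** There are three linked problems.

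1. The stated check has no target. In a logistic model the variance changes with the fitted probability by construction, so unequal spread of residuals is not evidence against the model.
2. With 12 binary outcomes in four small cells, the likelihood often has no maximum at finite coefficients (separation). Ordinary software then prints a huge odds ratio with a meaningless Wald interval. The rule for leaving the model mentions neither separation nor non-convergence.
3. The rule is applied after the data are seen, with no definition of poor fit. It leads to a test that ignores the stratification factor, although the control procedure itself differs by etiology.

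At stake is whether the promised adjusted effect and interval can be produced, and whether the choice of analysis is fixed before the results are known.

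**Working it through.** **Inputs.** Blocks of 3 at 2:1 within etiology, with 9 Crohn's and 3 idiopathic participants, give these cells: Crohn's intervention 6, Crohn's control 3, idiopathic intervention 2, idiopathic control 1. Control healing is 50% (2/4). Intervention healing is 7/8 = 87.5%, or 8/8. No dropout before Month 3, as the plan assumes. Equal healing rates across etiologies and ordinary maximum likelihood are assumptions made here.

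**The plan's own figures.** The Clopper-Pearson lower bound for 8/8 is the 2.5% quantile of Beta(8,1), 0.631 (stated 0.63). Taking the Carlin-Louis interval as the equal-tailed 95% interval of the difference of two Beta(1,1)-prior posteriors, the lower bounds are −0.145 for 7/8 v 2/4 (stated about −0.14) and −0.008 for 8/8 v 2/4 (stated −0.01). All three reproduce.

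**Homoscedasticity.** At the planning rates the variances are 0.5 × 0.5 = 0.25 and 0.875 × 0.125 = 0.109. They are unequal whenever the treatment has an effect of this kind.

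**Existence of the estimate.** Every possible outcome in the four cells was enumerated. Separation for intercept + arm + etiology was tested by linear programming, and outcomes were weighted by their binomial probabilities, with control healing at 50%:

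| Intervention healing | Treatment odds ratio not finite | Any coefficient not finite |
|---|---|---|
| 50% | 17% | 35% |
| 70% | 23% | 43% |
| 80% | 34% | 53% |
| 87.5% | 50% | 66% |

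The 50% at the planning rates can be broken down:
- All 8 intervention patients heal: 0.875^8 = 0.344.
- Otherwise, all or none of the 4 controls heal: (1 − 0.344) × 2 × 0.5^4 = 0.082.
- Remaining separated patterns: 0.499 − 0.344 − 0.082 = 0.073.

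**The plan's scenarios.**
- 8/8 v 2/4: no intervention patient fails, so raising the arm coefficient always raises the likelihood. The odds ratio is not finite in any arrangement.
- 7/8 v 2/4: the treatment odds ratio is not finite in 12.5% of arrangements, and some coefficient is not finite in 50%.

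**What the residuals would show at 8/8 v 2/4.** If the idiopathic control heals, the limiting fitted values in the cells (order as above) are 1, 1/3, 1, 1. If not, they are 1, 2/3, 1, 0. Both equal the observed proportions exactly, so residuals show no lack of fit where the odds ratio does not exist.

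**Standardized risk ratio at 8/8 v 2/4.** The standardized control risk is (9/12)(1/3) + (3/12)(1) = 0.5, or (9/12)(2/3) + (3/12)(0) = 0.5. The limiting ratio is 1/0.5 = 2.0, which is finite.

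**Fallback.** Fisher's test gives p = 0.091 for 8/8 v 2/4 and 0.236 for 7/8 v 2/4. Its power at 87.5% v 50% is about 13%.

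**Under the fix.** Firth estimates with profile-likelihood intervals:
- 8/8 v 2/4: 15.4 (0.91 to 2928) or 17.8 (0.95 to 3174), depending on which controls heal.
- 7/8 v 2/4: 4.4 to 5.3 in three of the four possible splits, with intervals from about 0.43 to 114. In the fourth split, the one that maximum likelihood cannot estimate, 8.1 (0.49 to 1230).

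**The case against.** A reader might infer that the main efficacy estimate will usually not exist. The documents do not support that. The 66% includes the etiology term, which is not the reported effect. For the treatment odds ratio the chance is about even at the planning rates and well below that at lower intervention healing. The standardized risk ratio and the healed proportion in each arm are also planned and can survive separation.

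A reader might also infer that unequal variance itself triggers the switch. The literal trigger is poor fit. Homoscedasticity is one of two things inspected in the sentence before.

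Nor was the trial sized solely on a risk difference. Sample Size says that the number was influenced first by the primary outcome and also by healing. Making the difference the headline measure would be a preference.

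It is fair to say that no estimator is named, that the SAP is not shown, and that Statistical analysis allows alternative models when assumptions are doubtful. The SAP may well specify a penalized method. That would remove the separation problem, but it would not correct the stated check or the stated fallback.

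Finally, stratifying the exact test changes little at this size. For 8/8 v 2/4 it gives 3/36 = 0.083 if both control failures are Crohn's, or 1/3 × 1/3 = 0.111 if there is one in each etiology, against 0.091 unstratified. The case for stratifying is consistency with the design, not a different answer. The article also concedes limited power for efficacy.

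**Conclusion.** Wrong as written, on a secondary endpoint. Three things stand:

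- The homoscedasticity check names an assumption that the model does not make, and no unseen document can make that sentence correct.
- The switch is undefined, is judged after the data are seen, and may miss the failure most likely to occur. The test it leads to ignores etiology, out of line with the general adjustment rule and the stratified randomization, and gives no adjusted effect estimate.
- Under ordinary maximum likelihood the promised odds ratio is not finite in about half of trials at 87.5% v 50%, in 17% to 34% at intervention rates of 50% to 80%, and in every arrangement of 8/8 v 2/4, the more favourable of the plan's two healing scenarios.

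The percentages rest on cells of exactly 6, 3, 2 and 1, equal healing rates across etiologies and no dropout. With an even 6/6 etiology split, the treatment figure at the planning rates is 52%, so it does not depend on the expected mix. The primary endpoint is unaffected.

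**What to change.** Delete the homoscedasticity check and the poor-fit switch. Pre-specify one analysis: Firth-penalized logistic regression with arm and etiology, giving the adjusted odds ratio with a profile-likelihood interval and the standardized risk ratio. If a p-value is wanted, use an exact test stratified by etiology. Apply the same to Month 6 recurrence, which inherits the procedure. Optionally, also report the risk difference with the Carlin-Louis interval already used in Sample Size.

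The cost is wording, since the methods are in standard software. The trial is ongoing, so the change should be made before outcomes are analysed by arm. The downside is that the penalized odds ratio is shrunk and, as the Firth intervals above show, will be very wide at 12 participants. The change makes the estimate exist and fixes the analysis in advance. It does not make the result precise.

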### Statistical analysis

Categorical and binary data will be presented using counts and percentages. Continuous data will be presented using medians and interquartile ranges. All statistical tests will use an α = 0.05 Type I error rate, using two-tailed p-values as appropriate for the specified hypotheses, but 95% confidence intervals will be given primary focus above p-values (29). Statistical models will be adjusted for Crohn’s status. Model assumptions will be checked using visualizations and tests as appropriate, with data transformations and alternative models considered when assumptions are dubious.

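### Month 3 healing: the imputation rule makes no exception for withdrawal due to treatment failure, so a known failure can be imputed as healed

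*Protocol article*

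**What the plan says.** Three parts of the protocol article bear on this point.

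- **Secondary and Tertiary Outcomes Analysis, missing data.** For binary healing at Month 3 the general rule is "Missing data are expected to be limited but will be handled using multiple imputation". The next sentence extends it: "Individuals who are lost to follow-up before Month 3 will also be included via the multiple imputation procedure". The named predictors are baseline and Month 1 assessments and the weekly symptom data. The reason for withdrawal is not among them, and no reason is exempted.
- **Same section, definition.** The probability of healing in each arm is the share of randomized participants who are diagnosed as healed at the Month 3 visit. The analysis is by randomized arm, modified so that only those who received the implant are analysed in the intervention arm.
- **Participant Discontinuation/Withdrawal from the Study.** The investigator may withdraw a participant for, among other reasons, infection or abscess leading to plug removal and a routine care procedure, an unacceptable adverse event, or disease progression that ends the study intervention. Loss to follow-up is listed separately.

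The Sample Size section plans for none of this: "We assumed that study dropout before Month 3 will not occur".

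**The concern.** A participant whose implant had to be taken out, or whose disease progressed, has an outcome that is known in substance: the allocated treatment did not heal the fistula. The text offers two ways for that person to count as a success. If withdrawal means that no Month 3 examination takes place, the outcome is missing and goes to imputation, where some or all of the imputed values may be healed. If the person stays in the study and the replacement procedure works, the Month 3 examination finds no drainage and the healing is credited to the arm of randomization.

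The definition of the arm proportion also sits uneasily beside the imputation rule. Taken literally, it leaves a withdrawn participant in the denominator and out of the numerator. The proportion and the logistic model could then give different answers for the same endpoint. In a trial of 12, one such case is visible in the result.

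**Working it through.** **Inputs.** From Sample Size: 12 randomized 2:1, so 8 and 4; control healing 2/4; intervention scenarios 7/8 and 8/8, with stated lower limits for the difference of about −0.14 and −0.01. From Randomization and Blinding: 9 Crohn's and 3 idiopathic participants expected, in blocks of 3 within etiology. The probability q that a withdrawn failure is imputed as healed is not in the documents. It is an assumption, shown at 0.25, 0.5 and 1.

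**1. The plan's own figures.** The Clopper-Pearson lower limit for 8/8 is 0.025^(1/8) = 0.631 (stated 0.63). For the difference I took the Carlin-Louis interval as the equal-tailed 95% interval from two independent beta posteriors with uniform priors: 7/8 gives Beta(8,2), 8/8 gives Beta(9,1) and 2/4 gives Beta(3,3). Simulation with 4 million draws gives lower limits of −0.145 and −0.008, in line with the stated values. A Beta(0.5,0.5) prior gives −0.131 and +0.036 and fits less well. The planning figures are therefore sound, and the issue is only how failures enter the endpoint.

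**2. Two rules for one person.** Take a participant withdrawn at week 6 after implant removal, with no Month 3 visit. Under the arm-proportion definition the person was not diagnosed as healed, so contributes 0. Under the missing-data rule the person contributes q on average.

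**3. Size per case.** With h observed healed, k withdrawn failures and n in the arm, counting failures as not healed gives h/n. Imputing gives (h + kq)/n on average. The difference is kq/n.

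| q (assumed) | one case of 8: q/8 | one case of 4: q/4 |
|---|---|---|
| 0.25 | 3.1 points | 6.3 points |
| 0.5 | 6.3 points | 12.5 points |
| 1 | 12.5 points | 25 points |

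**4. On the plan's own scale.** These are the extremes, not healed against healed in every imputation:

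- Seven healed and one withdrawn failure in the intervention arm, control 2/4: 7/8 with lower limit −0.145, against 8/8 with −0.01.
- Six healed, one not healed and one withdrawn failure, control 2/4: 6/8 with −0.26, against 7/8 with −0.145.
- The withdrawn failure is a control, intervention 7/8: control 2/4 with −0.145, against 3/4 with −0.27.

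The first line is the full distance between the plan's two scenarios, "If 7 of the 8 intervention arm patients achieve healing" and "if all 8 intervention arm patients achieve healing, the expected interval lower bound will be −0.01". The third shows that the shift can also go against the intervention.

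**5. Who can have a plug removed.** Nine Crohn's participants make 3 blocks (6 intervention, 3 control) and three idiopathic make 1 block (2 intervention, 1 control). All 8 intervention participants have an implant. Among controls only idiopathic participants receive a plug, so about 1 of 4.

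**The case against.** The strongest defence has five parts.

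- The sentence on loss to follow-up does not name the failure reasons, and the withdrawal list keeps the two apart. This is correct. Failures reach imputation only through the general sentence before it, but that sentence has no exception.
- The arm-proportion definition already treats a withdrawn participant as not healed. Read literally it does, but the adjusted odds ratio and marginal risk ratio come from the logistic model, to which the imputation rule is attached. The two need reconciling.
- Withdrawal is optional, recorded adverse events are followed until resolution, and nothing says that the Month 3 examination is forgone. This stands as a limit: the imputation route needs a missing visit. The other route, healing after a replacement procedure, does not.
- Imputation uses Month 1 and weekly symptoms, and the survey records leakage. Poor symptoms would lower q, but nothing sets it to zero.
- The endpoint is secondary, the primary outcome already fails anyone with an intervention-related serious adverse event within 3 months, and the unseen SAP may carry the exception. This limits the weight of the point. It does not alter the rule that the article states.

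Four stronger readings are tempting, and the documents do not support them.

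- **The rule favours the intervention.** The plug-removal route does apply mainly to that arm, but the adverse-event and progression reasons are not written for one arm only, and a control case weighs twice as much. With a uniform prior and no symptom information, one failure beside 7/7 healed gives 8/9 × 12.5 = 11.1 points in the intervention arm. One beside 2/3 healed gives 3/5 × 25 = 15 points in the control arm.
- **A true 87.5% would be reported as about 99%.** That is (7 + 8/9)/8, and it ignores the planned conditioning on symptoms.
- **Month 6 retention is capped at 75%.** Withdrawal for failure to heal at Month 3 is optional, and unhealed controls may cross over and continue visits.
- **Imputation cannot be fitted with 12 people.** Nothing requires each weekly survey to be a separate predictor, and the model's specification can be left to the SAP.

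**Conclusion.** The point holds as a gap and an inconsistency in the analysis rule for a secondary endpoint. As written, missing Month 3 healing is imputed regardless of reason. A participant withdrawn because the treatment failed can therefore be counted as wholly or partly healed, while the arm proportion read literally counts the same person as not healed. Healing after a replacement procedure is credited to the allocated arm.

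Each imputed case inflates the healing proportion by q/8 in the intervention arm or q/4 in the control arm. Over the range shown, that is 3.1 to 12.5 and 6.3 to 25 percentage points. The net direction is not determined, because it depends on how many cases occur in each arm. The imputation figures assume that a withdrawn participant has no Month 3 visit, and that q, which the documents do not give, is above zero. The planning limits of −0.14 and −0.01 serve only as a yardstick: both intervals include zero, and the endpoint itself is analysed by logistic regression.

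**What to change.** This is an analysis change only. State that implant removal, another fistula procedure, or withdrawal for infection, disease progression or a treatment-related adverse event before Month 3 counts as not healed. Apply the rule in both arms, and in both the arm proportion and the logistic model, so that the two agree. Keep multiple imputation for outcomes missing for unrelated reasons, and add best-case and worst-case bounds for those as a sensitivity analysis.

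The cost is a few sentences in the protocol and SAP. The reported healing rate may be slightly lower. No visit, procedure or withdrawal criterion changes.
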